## Abstract

**Background -:**

Experimental studies have shown that ultrasound contrast agents enhance the effectiveness of thrombolytic agents in the presence of ultrasound *in vitro *and *in vivo*. Recently, we have launched a clinical pilot study, called "Sonolysis", to study this effect in patients with ST-elevation myocardial infarction based on proximal lesions of the infarct-related artery.

**Methods/design -:**

In our multicenter, randomized, placebo controlled clinical trial we will include patients between 18 and 80 years of age with their first ST-elevation myocardial infarction based on a proximal lesion of the infarct-related artery. After receiving a single bolus alteplase 50 mg IV (Actilyse^® ^Boehringer Ingelheim GmbH), a loading dose of aspirin 500 mg, and heparin 5000 IU in the ambulance according to the prehospital thrombolysis protocol, patients, following oral informed consent, are randomized to undergo 15 minutes of pulsatile ultrasound with intravenous administration of ultrasound contrast agent or placebo without ultrasound. Afterwards coronary angiography and, if indicated, percutaneous coronary intervention will take place. A total of 60 patients will be enrolled in approximately 1 year.

The primary endpoints are based on the coronary angiogram and consist of TIMI flow, corrected TIMI frame count, and myocardial blush grade. Follow-up includes 12-lead ECG, 2D-echocardiography, cardiac MRI, and enzyme markers to obtain our secondary endpoints, including the infarct size, wall motion abnormalities, and the global left ventricular function.

**Discussion -:**

The Sonolysis study is the first multicenter, randomized, placebo controlled clinical trial investigating the therapeutic application of ultrasound and microbubbles in acute ST-elevation myocardial infarction patients. A positive finding may stimulate further research and technical innovations to implement the treatment in the ambulance and maybe obtain even more patency at an earlier stage.

**Trial registration -:**

Trialregister NTR161

## Background

Thrombo-occlusive cardiovascular disease is the leading cause of mortality in the western world. Among these, acute ST-elevation myocardial infarction (STEMI) is an important disease with high morbidity and mortality. In the course of years, two major treatment strategies have been developed, aiming at immediate restoration of coronary blood flow.

Currently, the first choice of treatment in patients with acute STEMI is primary percutaneous coronary intervention (PCI). However, its feasibility depends on the availability of equipment and trained personnel. As a result, thrombolysis is worldwide the most commonly used therapy for patients with STEMI[1]. Nevertheless, thrombolysis is known to have a relatively low recanalization rate and is related to more haemorrhagic complications[2].

Hence, there is an ongoing search for a non-invasive and easy applicable therapeutic strategy with less serious side-effects, still based on the early restoration of coronary blood flow.

One of the new non-invasive therapy strategies is the use of ultrasound and an ultrasound contrast agent, in combination with thrombolysis[3,4].

Previous studies have indicated that ultrasound alone may accelerate fibrinolysis[5]. The addition of microbubbles being destroyed by high pressure ultrasound leads to an even greater increase of fibrinolysis. There are three proposed mechanisms which lead to this increase. The first is the occurrence of shear stress based on micro-jets which are created after the destruction of the microbubbles by ultrasound[6]. The second mechanism is the generation of reactive oxygen species in endothelial cells[7]. The third proposed mechanism for the increase of fibrinolysis is temperature rise which also takes place after the microbubbles collapse under influence of ultrasound[8]. Although the full mechanism remains to be resolved, the application of ultrasound alone and ultrasound in combination with contrast agents have proven their value by enhancing clot dissolution, by creating microholes in fresh thrombi. Tachibana and Tachibana were among the first to describe the effect of an ultrasound contrast agent on fibrinolysis *in vitro*[9]. They added urokinase with microbubbles (Albunex) and ultrasound, which led to a significant increase in fibrinolysis. This result was confirmed by other *in vitro *studies in the course of years [10-13] (Table 1).

**Table 1 T1:** Studies assessing the influence of microbubbles and ultrasound on thrombolysis

Author(s)/reference	Microbubble	Target *in vivo*/*in vitro*	TL, US, MB	US frequency	Outcome
Tachibana and Tachibana[9]	Albumin MB (albunex)	*In vitro *thrombus	UK, US and MB	170 kHz, 0.5 W/cm^2^	Significantly increased thrombolysis with thrombolytics, US and MB
Kondo et al. [10]	Air-filled MB with galactose/palmitic acid shell	*In vitro *white thrombus	t-PA, US and MB	10 MHz, 0.5–1.0 W/cm^2^	Significant enhancement of thrombus reduction by MB
Nishioka et al. [11]	DDFP	*In vitro *and *in vivo *canine iliofemoral arteries	MB and US	20 kHz, 1.5 W/cm^2^	Increased clot disruption and recanalization with US and MB
Porter et al. [12]	Air-filled MB/PESDA MB	*In vitro *thrombus	UK, US and MB	20 kHz, 40 W/cm^2^	Significant better thrombolysis of PESDA than air-MB. Optimal thrombolysis with UK and MB
Mizushige et al. [13]	Albumin Shell, air-filled/galactose shell air-filled/DDFP-filled MB	*In vitro *thrombus	t-PA, US, MB	10 MHz, 1.02 W/cm^2^	Thrombolysis was greatest in DDFP-MB-group
Birnbaum et al. [14]	PESDA MB	*In vivo *canine iliofemoral artery	US and MB	Up to 160 W/cm^2^	Significant higher recanalization rate with MB
Siegel et al. [15]	DDFP/PESDA	*In vivo *rabit iliofemoral artery and canine LAD	SK, US, MB	20–37 kHz, 1.5–160 W/cm^2^	Increased clot dissolution with US, MB and SK
Culp et al. [16]	PESDA tagged with eptifibatide	*In vivo *pigs ascending pharyngeal artery	US and MB	1 MH, 2 W/cm^2^	Improvement of recanalization rate in eptifibatide tagged PESDA
Xie et al. [17]	Definity	*In vivo *canine femoral artery and vein	US and MB	1 MHz, 0.4–0.6 W/cm^2 ^and 10 W/cm^2^	Higher recanalization rates with MB and US compared to US alone
CLOTBUST investigators[18]	-	*In vivo *middle cerebral artery Phase 2 trial	t-PA and US	2 MHz	Ultrasound augments t-PA induced arterial recanalization
Molina et al. [19]	Galactose MB (Levovist)	*In vivo *middle cerebral artery phase 2 trial	t-PA, US, MB	2 MHz	MB safely induces acceleration of US enhanced thrombolysis
Cohen et al. [20]	-	*In vivo *STEMI phase 2 trial	rt-PA and US	27 kHz	No major adverse events

MB = microbubble; US = ultrasound; TL = thrombolytic; (r)t-PA = (recombinant) tissue plasminogen activator; PESDA = perfluorocarbon-exposed sonicated dextrose albumin; UK = urokinase; DDFP = dodecafluoropentane; LAD = left artery descending; SK = streptokinase

Birnbaum et al. were among the first to conduct an *in vivo *study[14]. They used rabbit iliofemoral arteries to examine the effect of ultrasound and microbubbles on fibrinolysis, without using any fibrinolytics. The recanalization rate in the artery treated with a combination of microbubbles and ultrasound was significantly higher compared to the application of ultrasound or microbubbles alone.

Siegel et al. conducted an other *in vivo *study in rabbit iliofemoral arteries[15]. They showed a significant increase of fibrinolysis in the combination of streptokinase and ultrasound compared to streptokinase alone. Adding microbubbles did not made any difference, however the combination of the three was still better then streptokinase alone.

Other *in vivo *studies confirmed a higher recanalization rate using ultrasound and microbubbles[16,17] (Table 1).

In 2004, the CLOTBUST investigators published results of a multicenter phase II trial conducted in patients with acute stroke[18]. They randomly assigned 126 patients to receive continuous ultrasound or placebo following treatment with intravenous t-PA (0.9 mg/kg with a maximum of 90 mg) within 3 hours after the onset of symptoms. The results within 2 hours after administration showed a significant increase of complete recanalization in the ultrasound group compared to placebo. It also showed a nonsignificant trend towards recovery from stroke, compared with placebo.

Molina et al. conducted a trial in which they added microbubbles on top of ultrasound and t-PA[19]. The addition of microbubbles induced further enhancement of ultrasound augmented thrombolysis, leading to more complete recanalization.

The first to conduct a study in which ultrasound and thrombolytic therapy was combined in a small group of STEMI patients were Cohen et al. They found no major adverse events and regarding efficacy their outcome compared favourably with historical data[20].

However, until now the combination of ultrasound, ultrasound contrast agents (UCA), and thrombolytic therapy has never been tested in STEMI patients. Therefore, we will perform the first study in a pilot design in patients with STEMI, in which we compare the combination of ultrasound and microbubbles with placebo after prehospital thrombolysis.

## Methods and design

### Study design

Sonolysis is designed as a multicenter, randomized, placebo controlled clinical trial that will be conducted in the VU University Medical Center Amsterdam, University Medical Center Utrecht, and Radboud University Nijmegen Medical Center.

We will include patients between 18 and 80 years of age with an acute STEMI based on a proximal lesion. To make sure that we deal with a blocked proximal major epicardial coronary artery our inclusion criteria consist of a sum of ST-elevation of 6 mm or more in combined leads and 1 mm or more ST-elevation in lead V3R when there is an inferior infarct. The exclusion criteria are mentioned in Table 2.

**Table 2 T2:** Exclusion criteria of the Sonolysis study

• Clinical instability	
• Previous Q-wave myocardial infarction	
• Contra indications alteplase (Table 3)	
• Known pulmonary hypertension (> 90 mmHg)	
• Known allergy of Luminity^®^	

Patients are randomized in either a placebo group or a group that receives the ultrasound contrast agent Luminity^®^.

Randomization will take place on announcement by the ambulance of a patient with an eligible STEMI. This announcement is done through the unique Lifenet system. An ECG of a patient with chest pain is recorded by ambulance personnel and sent to a computer in the coronary care unit of the hospital. There, the cardiology resident on call consults the intervention cardiologist and together they will check the ECG for the inclusion criteria. If the patient is eligible for the study, the ambulance personnel will be informed. This all is summarised in a flow chart (Figure 1)

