**Figure 1 F1:**
[figure not shown]
Flow chart of the study design, divided in a hospital and a pre- hospital part.

Randomization will be done by opening a sealed envelope containing the contrast agent Luminity^® ^or saline 0.9%, the placebo.

Patients will be pre-treated in the ambulance with a loading dose of aspirin 500 mg iv., heparin 5000 IU iv., and a single bolus alteplase 50 mg IV (Actilyse^® ^Boehringer Ingelheim GmbH). The latter will be administered in approximately 3 minutes if there are no contra-indications (Table 3). This is in accordance with the prehospital thrombolysis protocol[21,22].

**Table 3 T3:** Contraindications alteplase.

• Reduced consciousness	
• Paralysis	
• Arterial hypertension (systolic pressure > 180 mmHg)	
• Known or suspected haemorrhagic diathesis	
• Possible pregnancy	
• Any history of stroke	
• In the **past 3 months**	
◦ Significant trauma	
◦ Major surgery	
◦ Haemoptysis	
◦ Documented ulcerative gastrointestinal disease	
◦ Manifest or recent severe or dangerous bleeding	
• Allergy to streptokinase or t-PA	
• Systolic blood pressure of less than 80 mmHg during more than 5 minutes with clinical symptoms of shock	

To avoid any time delay, informed consent will be obtained orally, prior to PCI at arrival in the hospital. Written informed consent will be given after primary PCI when the patient is in a stable clinical condition.

At arrival in the hospital, patients receive, after oral informed consent, either placebo (i.e. 50 ml saline 0.9%) without ultrasound, or the ultrasound contrast agent Luminity^® ^during simultaneously pulsatile ultrasound application.

We will use one flacon Luminity^® ^of 1.5 ml which contains 225 microliter perflutren, a high-molecular-weight gas, which increases the stability of the microbubbles. This will be shaken in the Vialmix™ for 45 seconds, to produce the microspheres. After that 48.5 ml of saline 0.9% will be added to create a 50 ml milky white suspension. The suspension or placebo will be administered intravenously in 15 minutes with an infusion rate of 200 ml/h.

Luminity^® ^is registered in the Netherlands as a diagnostic contrast agent to improve imaging quality during echocardiography. Most occurring complications are minor, like headache (2.0%), flushing (1.0%), and back pain (0.9%). Allergic reactions happen approximately in one of every 10.000 patients[23].

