### Statistical analysis

The aim of this pilot study is to investigate whether the combination of ultrasound and microbubbles enhance clot dissolution after pre-treatment of STEMI patients with a loading dose of aspirin 500 mg, heparin 5000 IU, and alteplase single bolus 50 mg.

The reason we use a single bolus alteplase is to avoid serious adverse events. The PACT-trial[26] showed there was no difference in severe complications between the placebo group and the single bolus alteplase group after pre-treatment with aspirin and heparin, but there still was a significant increase in TIMI 3 flow in the alteplase group (33%) compared to placebo (15%). With our study we are aiming for 65% TIMI 3 flow in the group treated with microbubbles. In order to demonstrate this with a power of 80% and an α of 0.05 (two sided) we need a sample size of 29 patients per group. Therefore, we are intending to randomize 60 patients in this pilot study.

Obtained baseline data will be presented as mean ± standard deviation (SD). Differences between the treatment group, with ultrasound and microbubbles, and the control group in baseline data, biomarkers, 2D-echo, and MRI variables will be assessed by unpaired students t-test.

Chi-square analyses will be conducted to observe differences in primary and secondary endpoints between the treatment group and the control group.

All analysis will be performed based on an intention-to-treat principle.

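### The Methods randomise at the ambulance call, before oral consent, and the Abstract randomises after it; under the Methods order every oral refusal follows an open allocation

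*Protocol article*

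**What the plan says.** The protocol article dates randomisation twice.

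- **Methods and design, Study design:** "Randomization will take place on announcement by the ambulance of a patient with an eligible STEMI". The check described at that moment is that the resident and the intervention cardiologist look at the transmitted tracing: "together they will check the ECG for the inclusion criteria".
- **Same section, text after Figure 1:** "Randomization will be done by opening a sealed envelope containing the contrast agent" or saline. Opening the envelope is therefore both the act of randomising and the moment the arm becomes known.
- **Same section, on consent:** "informed consent will be obtained orally, prior to PCI at arrival in the hospital". Written consent comes later: "Written informed consent will be given after primary PCI when the patient is in a stable clinical condition". Treatment follows oral consent: "At arrival in the hospital, patients receive, after oral informed consent, either placebo" or contrast agent with ultrasound.
- **Abstract, Methods/design:** after the ambulance drugs, "patients, following oral informed consent, are randomized to undergo 15 minutes of pulsatile ultrasound" with contrast agent, or to placebo.
- **Statistical analysis:** "All analysis will be performed based on an intention-to-treat principle".

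**The concern.** Randomisation cannot come before arrival at the hospital and also follow a consent that is given at arrival. The two statements are both current text, so staff cannot follow both.

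The order matters because the allocation is not masked once the envelope is open. One arm receives a milky suspension with ultrasound, the other receives saline with none. If the envelope is opened at the ambulance call, every patient who then declines does so after the arm has been revealed. Two things can follow. If refusers are left out, the analysed groups are no longer the randomised groups, and the loss may differ by arm because the arm was known. If refusers are kept in their assigned group without study treatment, the comparison stays randomised but the observed effect shrinks. If the envelope is opened after oral consent, oral refusals fall before allocation and neither problem arises from them.

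**Working it through.** **Sequence of events.**

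| Step | Methods and design | Abstract |
|---|---|---|
| 1 | Ambulance call; envelope opened, arm known | Ambulance drugs given |
| 2 | Arrival; oral consent sought | Oral consent |
| 3 | Study treatment | Randomisation, then study treatment |
| 4 | Angiography (primary endpoints), PCI if indicated | Angiography, PCI if indicated |
| 5 | Written consent | Not mentioned |

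The Methods sentence that puts treatment after oral consent dates the treatment, not the randomisation, so it does not remove the conflict.

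**Inputs for the size.** From the Statistical analysis section: control rate p1 = 0.33, target rate p2 = 0.65, two-sided α = 0.05, power 80%, 29 per group, 60 randomised (30 per arm). The refusal rate r is not given; 10% and 20% in each arm are assumptions.

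**The plan's own figure.** The formula for a two-sided comparison of two proportions is

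n = [1.96·√(2·p̄·(1−p̄)) + 0.8416·√(p1(1−p1) + p2(1−p2))]² / (p2−p1)²

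With p̄ = 0.49, the two roots are √0.4998 = 0.7070 and √0.4486 = 0.6698, so n = (1.3856 + 0.5637)² / 0.1024 = 37.1, or 38 per group. The stated 29 is not reproduced. A one-sided calculation gives 30. This is a separate issue; it only explains why the starting power below is not 80%.

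**Power formula.** Power = Φ{[(p2−p1)·√n − 1.96·√(2·p̄·(1−p̄))] / √(p1(1−p1) + p2(1−p2))}.

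- No refusals, n = 30: (0.32 × 5.477 − 1.3856) / 0.6698 = 0.548, power 70.8%.
- **Dropped**, equally in both arms and unrelated to outcome:
  - r = 10%, n = 27: (0.32 × 5.196 − 1.3856) / 0.6698 = 0.414, power 66.1%.
  - r = 20%, n = 24: (0.32 × 4.899 − 1.3856) / 0.6698 = 0.272, power 60.7%.
- **Kept untreated**, with refusers in the active arm responding at the control rate, n = 30:
  - r = 10%: rate 0.9 × 0.65 + 0.1 × 0.33 = 0.618, power 61.3%.
  - r = 20%: rate 0.8 × 0.65 + 0.2 × 0.33 = 0.586, power 51.2%.

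**Selective loss.** Suppose there is no true effect and each arm has 33% of 30, that is 9.9 expected patients with TIMI 3 flow. Losing three patients without TIMI 3 flow from one arm moves it to 9.9/27 = 36.7%. Losing three with TIMI 3 flow moves it to 6.9/27 = 25.6%. These are extremes for a 10% loss in one arm, and a larger sample would not cure such a bias.

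**The case against.** The best defence is that this is a wording slip in a condensed article. No text has anyone receiving study treatment before oral consent. The consent process was shaped to avoid delay, so early randomisation may be deliberate. Rules for analysis sets usually sit in a fuller protocol or analysis plan, which is not shown. Figure 1, which is split into pre-hospital and hospital parts, is not visible either and may settle the sequence. All of this is fair, and it limits the claim. It does not reconcile two positive statements that give opposite orders.

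A reader might infer more than the document supports:

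- *That patients are randomised on the ECG alone and found ineligible later.* The article speaks of an eligible STEMI and does not say when the Table 2 exclusions are checked. The alteplase contraindications, which are one of those exclusions, are tied to the ambulance drug step, and known allergy or known pulmonary hypertension could be asked about before arrival. Late ineligibility is only a possible added concern.
- *That the person seeking consent knows the arm.* No text says who opens the envelope or who asks for consent. The allocation is open, so the risk is plausible, but it is not documented.
- *That refusers cannot be analysed, so intention to treat cannot be kept.* No rule on their data is stated. The primary endpoints come from the standard emergency angiogram, so they may exist for refusers. The damage depends on how refusers are handled.
- *That this conflict explains the shortfall from 80% power.* It does not; that shortfall is present with no refusals at all.

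**Conclusion.** The conflict over the order of oral consent and randomisation is established from the text and rests on no assumption. Its consequence is conditional: it arises only if the Methods order is the one followed, and its form depends on whether refusers are dropped or kept.

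The loss of power due to this point is about 5 percentage points (dropped) or 10 (kept) at an assumed 10% refusal, and about 10 or 20 at 20%, from a start of 71%. The true refusal rate is unknown. Selection bias would be additional and cannot be sized from the document beyond the extremes shown. The order of randomisation and consent decides who belongs to the randomised comparison, so it should be settled before enrolment.

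**What to change.** Reconcile the Abstract and the Study design section to one order:

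1. The ambulance call triggers screening and preparation only.
2. The envelope is opened at the hospital after oral consent and after confirming that no Table 2 exclusion applies, immediately before the infusion is prepared.
3. Every patient whose envelope was opened is analysed in the assigned group.
4. Figure 1 is checked for agreement with this order.

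The text change is small. In practice a short preparation step moves to after arrival: shaking the vial takes 45 seconds, and the article gives no time for the dilution that follows. Consent itself adds no delay, because the Methods already require it at arrival and before study treatment. The change does not remove every post-allocation loss. Written consent comes after PCI under either order, so withdrawal at that point remains possible.

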**Figure 1 F1:**
[figure not shown]
Flow chart of the study design, divided in a hospital and a pre- hospital part.

Randomization will be done by opening a sealed envelope containing the contrast agent Luminity^® ^or saline 0.9%, the placebo.

Patients will be pre-treated in the ambulance with a loading dose of aspirin 500 mg iv., heparin 5000 IU iv., and a single bolus alteplase 50 mg IV (Actilyse^® ^Boehringer Ingelheim GmbH). The latter will be administered in approximately 3 minutes if there are no contra-indications (Table 3). This is in accordance with the prehospital thrombolysis protocol[21,22].

**Table 3 T3:** Contraindications alteplase.

• Reduced consciousness	
• Paralysis	
• Arterial hypertension (systolic pressure > 180 mmHg)	
• Known or suspected haemorrhagic diathesis	
• Possible pregnancy	
• Any history of stroke	
• In the **past 3 months**	
◦ Significant trauma	
◦ Major surgery	
◦ Haemoptysis	
◦ Documented ulcerative gastrointestinal disease	
◦ Manifest or recent severe or dangerous bleeding	
• Allergy to streptokinase or t-PA	
• Systolic blood pressure of less than 80 mmHg during more than 5 minutes with clinical symptoms of shock	

To avoid any time delay, informed consent will be obtained orally, prior to PCI at arrival in the hospital. Written informed consent will be given after primary PCI when the patient is in a stable clinical condition.

At arrival in the hospital, patients receive, after oral informed consent, either placebo (i.e. 50 ml saline 0.9%) without ultrasound, or the ultrasound contrast agent Luminity^® ^during simultaneously pulsatile ultrasound application.

We will use one flacon Luminity^® ^of 1.5 ml which contains 225 microliter perflutren, a high-molecular-weight gas, which increases the stability of the microbubbles. This will be shaken in the Vialmix™ for 45 seconds, to produce the microspheres. After that 48.5 ml of saline 0.9% will be added to create a 50 ml milky white suspension. The suspension or placebo will be administered intravenously in 15 minutes with an infusion rate of 200 ml/h.

Luminity^® ^is registered in the Netherlands as a diagnostic contrast agent to improve imaging quality during echocardiography. Most occurring complications are minor, like headache (2.0%), flushing (1.0%), and back pain (0.9%). Allergic reactions happen approximately in one of every 10.000 patients[23].

The dose of 1.5 ml Luminity^® ^has been shown to be safe and well tolerated. Thus, we expect no difference in adverse events between both groups.

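### As worded, the randomisation envelope contains the study product itself, so the next allocation could be recognised by feel or weight before it is opened

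*Protocol article*

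**What the plan says.** All of this is in the protocol article, Methods and design, Study design, including the text that follows Figure 1.

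- **Device.** "Randomization will be done by opening a sealed envelope containing the contrast agent" Luminity or, for controls, saline 0.9%.
- **Active product.** It is supplied as one vial "of 1.5 ml which contains 225 microliter perflutren". It is shaken for 45 seconds, and dilution comes next: "After that 48.5 ml of saline 0.9% will be added to create a 50 ml milky white suspension".
- **Control.** Patients receive "either placebo (i.e. 50 ml saline 0.9%) without ultrasound".
- **Eligibility.** At the receiving hospital "the cardiology resident on call consults the intervention cardiologist and together they will check the ECG for the inclusion criteria".
- **Timing.** "Randomization will take place on announcement by the ambulance of a patient with an eligible STEMI".

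The article does not say who stores or opens the envelopes, how the saline is packed, or whether an active pack also holds its diluent.

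**The concern.** A sealed envelope conceals an allocation only if one envelope cannot be told from another. A seal stops someone reading a card, but it does not stop someone feeling or weighing a glass vial. If the envelope really holds the product, the outside may give away the next arm.

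Whoever knows the next arm and also influences entry can include or pass over a borderline patient according to that arm. The groups then differ at baseline for a reason unrelated to chance. The Statistical analysis section adopts the intention-to-treat principle, but that protects only against changes after randomisation, not against selective entry.

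The safeguard carries more weight here than in a fully masked trial. Controls get no ultrasound, so the treating staff know the arm once treatment starts, and two of the three primary endpoints (TIMI flow grade and myocardial blush grade) are visual grades. Concealment before entry is therefore one of the main protections left.

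**Working it through.** **1. What the envelope would hold, read literally**

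| | Active | Placebo |
|---|---|---|
| As supplied | 1.5 ml vial | saline 0.9%, pack not described |
| Added later | 48.5 ml saline | nothing stated |
| As infused | 1.5 + 48.5 = 50 ml, milky white | 50 ml saline |

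The infused volumes agree with the stated infusion: 200 ml/h × 15/60 h = 50 ml. So the arms match in volume at infusion. They need not match at the time that counts for concealment, when the envelope is still sealed. The active product cannot be packed ready-mixed to look like placebo, because the vial is shaken first and diluted afterwards, and the mixture is milky. If the active pack also held its 48.5 ml of saline, the total volumes would be equal, but the pack would still contain an extra vial.

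**2. Who could act on it**

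The resident on call and the intervention cardiologist check the ECG against the entry criteria, and randomisation follows the ambulance announcement. The ECG rule is numeric (summed ST-elevation of 6 mm or more, and 1 mm or more in V3R for an inferior infarct). Clinical instability, an exclusion in Table 2, is given no definition there and leaves room for judgement. The article neither says that these doctors handle the envelopes nor keeps the envelopes away from them.

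**3. What selection would cost (illustration)**

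Inputs from the article: 60 patients, hence 30 per arm; two-sided α of 0.05; chi-square test; 33% TIMI 3 flow with single-bolus alteplase. Assumptions: no true treatment effect, a mean rate across the arms held at 33%, and a gap g between the arms' underlying rates that arises from selection alone.

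The rejection probability is the sum of Bin(x; 30, 0.33 − g/2) × Bin(y; 30, 0.33 + g/2) over all pairs (x, y) with |z| > 1.96, where z is the pooled two-proportion statistic without continuity correction.

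| Assumed gap g | True rates | Rejects |
|---|---|---|
| 0 | 33% / 33% | 4.8% |
| 5 points | 30.5% / 35.5% | 6.7% |
| 10 points | 28% / 38% | 12.6% |
| 15 points | 25.5% / 40.5% | 22.9% |

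At 10 points, 12.3 of the 12.6 percentage points fall in favour of the advantaged arm.

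**4. How much steering a gap needs**

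If k patients in one arm are steered, and each differs by d in the probability of TIMI 3 flow from the patient replaced, then g = (k/30) × d, so k = 30g/d.

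- Upper bound, d = 100 points: one patient moves the arm by 1/30 = 3.3 points, and a 10-point gap needs k = 3.
- With an assumed d = 20 points: a 5-point gap needs k = 7.5, a 10-point gap k = 15 and a 15-point gap k = 22.5.

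The upper bound would require near-certain prediction of the angiogram before the patient arrives. With a modest d, the larger gaps need extensive steering.

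**The case against.** The strongest answer is that the sentence is loose English for an envelope that names the arm. The article has other awkward phrasing, and 50 ml of saline in an envelope is an odd arrangement. This is a fair reading and cannot be excluded. It changes what has to be done (correct a sentence or repack envelopes), but it does not make the present wording acceptable, because a site that follows it literally would put product in the envelope.

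Second, comparing a 1.5 ml vial with 50 ml of saline sets one product as supplied against the other as given. This also stands in part. The article does not describe the saline pack or say whether diluent travels with the vial. Differences in size and weight are therefore an inference from the wording, although a shaken-then-diluted vial is hard to make indistinguishable from plain saline.

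Third, a reader might infer that the doctors who decide eligibility can tell the next arm, so that allocation is predictable in this trial. The article does not support that. It would need literal packing, distinguishable packs, and access by those doctors before eligibility is settled, and none of the three is established. Part of the entry rule is also numeric, which narrows the room for steering.

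Finally, a condensed article may leave opacity, numbering and custody of envelopes to the full protocol. That is accepted, and their absence is not the point. The point is the positive statement about what the envelope contains.

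**Conclusion.** The concern holds as a risk created by the wording. Taken literally, the described mechanism puts physically different products in the envelopes, and the next allocation could be told before opening. No stated separation protects the eligibility decision from that knowledge. The documents do not show that any doctor can or will predict the allocation, nor that selection will occur.

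The documents give no size for the effect. Under the stated assumptions a selection gap of 5 points would raise the false-positive rate from 4.8% to 6.7%, and one of 10 points to 12.6%. The 15-point figure of 22.9% would probably need steering on a scale that is hard to credit. These figures show what selection would cost if it happened. The change is worth making because it is cheap, and because selection at entry cannot be corrected in the analysis.

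**What to change.** Replace the sentence on randomisation so that it says three things:

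1. The envelope holds only an allocation card, and envelopes are opaque and identical on the outside. Alternatively, allocation is by telephone or web.
2. The envelope is opened, or the call made, only after eligibility and the patient's identity have been recorded.
3. The Luminity vial or the saline is drawn from stock once the arm is known.

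If the present wording was only loose, the cost is one corrected sentence. If it is literal, about 60 envelopes must be repacked before enrolment. In either case each of the three sites needs a stock of vials and saline, and a short time is spent fetching the product. Remote allocation avoids the envelopes but depends on a line or system being available at any hour.
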